## Sample

A total population of singleton, Norwegian-speaking women will be invited after screening ultrasound in pregnancy week 17, exclusive pregnancies with severe anomalies or other cause to consider termination or non-Norwegian speaking/understanding women. Women will be recruited from hospitals not included in existing Femina collaboration. The period of inclusion should be intensive and as short as possible and in a geographical spread area, in order to minimize the potential contamination of information between participants, and to make the conditions for both health professionals and respondents as homogenous as possible.

Sample power analyses based on the preliminary observational study is done to estimate the number of respondents needed. The preliminary estimate with 80% power and a significance level of 0.05, is a total of 538 pregnancies in each arm of the trial. This will be further assessed after evaluation of the first part of the inclusion period.

## Recruitment of responders and data collection

Women will be recruited from the hospitals’ lists over women having been at the ultrasound screening in pregnancy week 17-19. A flow chart over data collection is appended (Appendix 1). All women will receive a letter in pregnancy week 23-24, asking to participate in a study of attitudes during pregnancy with a random possibility to be asked to perform FMC in the third trimester. Mothers, who agree to participate, do this by signing an informed consent and completing a baseline questionnaire (QI). On completion of the baseline inventories, but before inspection of the results, an assistant will perform the randomization into the FMC-group and the control group.

Women in the FMC-group will be asked to count fetal movements daily from gestational week 28. These women will be telephoned one week after commencement, to discuss questions or problems with the charting technique. Women in the control group will be told about the next survey at 34 weeks of gestation. Women in both groups will be asked to perform prospective, structured registrations – like a diary - if they were concerned about DFM and return these diaries to the study group after the delivery.

The questionnaires will be distributed in pregnancy weeks 24 (questionnaire I) and 34 (II). Answering the questionnaires can be done either by paper or by web-pages with interactive questions. An appropriate web-solution will be used for electronic data collection. Alternative retrieval for paper version: Scanning of questionnaires at the NIPH.

### Randomizing procedure

Randomization will be determined by computer-generated random allocation. The allocation of the responders will be blinded for the researchers and the recruiting midwife.

### Variables

The questionnaires will be developed to respond to the cited research questions in cooperation with a resource group for Femina; consisting of midwives, GP’s, obstetricians and pregnant women. When available, validated self-report psychometric scales are chosen.

### Psychometric Instruments

Where no Norwegian instruments were available, the English inventories (PAI and CWS), have been translated for this study into Norwegian by one of the researchers and back translated by another person, both fluent in English.

#### Mother-child attachment

Reviewing the literature, most studies measure MFA by the Maternal-Fetal Attachment scale (MFAS)39, less frequently used are Müller’s Prenatal Attachment Inventory (PAI)48 and Condon’s Maternal-Antenatal-Attachment Scale (MAAS)38. MFA as measured by these scales is consistently related to pregnancy planning, strength of the marital relationship, gestational age and maternal depressed mood41. The variables of maternal age, parity, self-esteem and socioeconomic status are inconsistently related to MFA across studies (Erikson 1996). Social support of family members and peers is a significant predictor of MFA; perceived support of prenatal care providers was correlated with MFA at 0.74, providing further evidence that psychosocial support is a critical component of prenatal care52. In spite of different framework in these three inventories, it has been shown correlation between the MFAS and PAI (r=0.41, p<0.001)44, and Condon’s scale has been assessed to be very similar to those reported by investigators using the MFAS42. The PAI is assessed to be the most suitable tool for measuring MFA and is chosen in this study; this inventory emphasizes affiliation rather than behavior and the psychometric properties remain quite adequate in the PAI, with high construct validity and reliability, total score Cronbach’s alpha was reported to be 0.8749;53. This instrument is designed to measure, from the mother’s perspective, the affectionate relationship that develops between a mother and her unborn baby and not merely the experience of pregnancy as a physical state or her appreciation of the tasks concerning the motherhood role48. The PAI is a 21-item inventory is rated on a 4-point Likert-type scale indicating how often the mother has affectionate thoughts or behaves affectionately toward the fetus. Individual items are summed and treated as ratio data. Higher scores indicate greater attachment. Measurements with the three inventories have mostly been performed in pregnancy week 33-36.

#### Maternal mood state

MFA is consistently related to maternal depressed mood41. Identification of depression prior to FMC is important to assess possible interactions with MFA. The 25-item Hopkins Symptom Checklist (HSCL-25) is a self-reporting inventory to obtain information on symptoms on emotional distress in normal populations54. A short version (SCL-8) has been developed at The Norwegian Institute of Public Health (unpublished), and contains for items for depression and four for anxiety. Both versions have 4-point Likert scales.

#### Self-efficacy

GSE (Generalised Self-Efficacy)55, has been shortened into a five-item scale and translated into Norwegian56 and includes 4-point Likert scales. GSE appears to be a universal construct that yields meaningful relations with other psychological constructs.

#### Self-esteem

The Rosenberg Self-Esteem scale(RSES)57 has been validated and translated into Norwegian and is recommended by the Norwegian Registry of Psychometric Scales51. On basis of recommendations here and in line with the Norwegian Mother and Child Cohort study58 a four-item scale of the RSES is chosen with 4-point Likert scales.

#### Maternal well-being

The Cambridge Worry Scale (CWS)59 has demonstrated good reliability and validity60, also in a Scandinavian population61. The measure contains 16 items, measuring women’s major worries during pregnancy in a four-factor structure; socio-medical, own health, socio-economic and relational aspects. Responses are made on a 6-point Likert-type scale (from 0=”not a worry” to 5=“extremely worried”). An open-ended question at the end allows the respondents to tell about other worries not in the list.

### Perinatal factors

#### Obstetric history

Obstetric history and pregnancy outcome will be obtained from copies of case notes. Questions about these issues and factors associated with MFA will be included in the surveys as covariates according to the overview.

#### Identification of perinatal risk factors in actual pregnancy

This study is not suited to use primary outcome measures which are frequent used in traditional epidemiological research on these topics. Earlier studies on research on fetal movements and the relevance and significance of FMC, consequently use primary outcomes as perinatal death, fetal growth restriction, severe fetal asphyxia, acute caesarean section, preterm birth and transfer to NICU. However, these “hard” and relatively rare outcomes are not useful for this study, since this study aims to register the mothers’ ability to identify significant changes of fetal activity, i.e. the number of identified pregnancies with a risk condition on basis of the mothers’ interpretation of fetal movements and management if significant changes. Therefore, the primary outcomes in this study are identification of risk pregnancies, e.g. number of consultations where an intervention or further observation was indicated on basis of the mothers’ perception of DFM.

Primary outcome measures – pathology identified according to Norwegian guidelines:

- Fetal growth restriction (FGR) identified by ultrasound prior to birth:
- FGR at birth, unidentified prior to birth
- Acute caesarean section on fetal indication (exclusive protracted delivery)
- Non–reactive non-stress test (NST)
- Oligohydramnios
- Pathologic flow in arteria umbilicalis
- Maternal perception of absent fetal movements for more than 24 hours before admission to hospital:
- Perinatal death

Secondary outcome measures:

- Frequency of consultations because of maternal concern
- Use of resources in evaluation of these pregnancies (NST, ultrasound, Doppler, recurrent consultations)
- Induced or spontaneous start of delivery
- Mode of birth

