The medicalization of perinatal care may have affected pregnant women’s view on own ability to recognize warning signals. However, the past several years, it seems to be an ongoing process against the medicalized perinatal care, and governmental reports in several countries have advised that women should be enabled to make and implement informed choices and the mothers have been increasingly encouraged to take an active part in making decisions regarding their care. In line with guidelines for antenatal care from WHO21 and NICE22, the new Norwegian guidelines for standard antenatal care also focus on demedicalization of pregnancy; with reduced frequency of standard antenatal controls and less tests23. Demedicalization in antenatal care implies to give the power back to the women, stimulate her listening to her body’s signals and improve the trust in non-instrumental signals. However, there seems to be a “missing link” – women are recommended fewer standard controls, but *without* receiving information and tools to be left with this responsibility. The mothers have not given relevant tools to be able to take care for their unborn child. This may affect their reporting of DFM and consequently time-consuming and frequently unnecessary investigations. We want to develop scientific knowledge on the pregnant women’s perception of FM and interpretation of significant changes in the FM pattern. Information and FMC could be a tool for getting to know their unborn child better, give the mothers a greater sense of control of her pregnancy and improve their ability to act on signs of complications at an optimal point of time.

The basic principle for antenatal care is to identify risk conditions where further observation or intervention is indicated in order to improve health for the mother or the child. An intervention may therefore be a positive action, e.g. if a CS is performed after a mother has experienced DFM and the child was in a threatened condition. Therefore, this study aims will be the number of identified risk pregnancies, not the end point of the pregnancies.

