# Aim and outcome measures

The aim is to test effects of using formal kick counting chart in the third trimester of pregnancy in an unselected population. The research questions are:

Does Fetal Movement Counting:

1. Improve the identification of risk pregnancies / pathology?

*Primary outcome measures*: Numbers of identified pathological conditions in pregnancies (fetal growth restriction (FGR), acute caesarean section on fetal indication/non–reactive non-stress test (NST), oligohydramnios, pathologic blood flow in arteria umbilicalis, maternal perception of absent fetal movements for more than 24 hours before admission to hospital, or perinatal death).

*Secondary outcome measures*: Frequency of consultations because of maternal concern, use of resources in evaluation of these pregnancies (NST, ultrasound, Doppler, recurrent consultations), induced or spontaneous start of delivery, mode of birth.

1. Affect the women’s well-being?

*Primary outcome measure*: Maternal concern.

*Secondary outcome measure:* Maternal satisfaction with use of FMC and sense of control in interpretation of signals from own body and child.

1. Stimulate maternal-fetal attachment antepartum?

*Primary outcome measure*: Maternal-fetal attachment.

*Secondary outcome measure:* Health promoting behavior in pregnancy (smoking habits, use of alcohol, attending standard program for antenatal care).

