## Identification of risk pregnancies

The goal is to increase the accuracy of maternal perception of DFM as a predictor for need of examination or intervention. This will be measured by a compound measure of rates of identification of risk pregnancies related to DFM. Prevalence of risk conditions are estimated from preliminary results of Femina (unpublished) or the Norwegian Birth Register.

| Condition | Prevalence |
| --- | --- |
| Fetal distress: Acute caesarean section on fetal indication (excl protracted birth), non-reactive NST, pathological levels of fetal scap-pH or Apgar5 min ≤ 3 | 8 % |
| Fetal growth restriction < 2.5 centile or pathological Doppler flow in arteria umbilicalis | 5 % |
| Absent fetal movements for more than 24 hours | 0.5 % |
| Intrauterine death | 0.02 % |
| Estimated prevalence of compound measure | 13.52 % |

The goal is a 10% increase of identification of these risk pregnancies, which gives an estimated sample of 538 in each arm of the trial with 80% power and a significance level of 0.05.

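### The primary compound counts growth restriction whether it was found or missed before birth, so better detection of it cannot move the outcome

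*Protocol*

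**What the plan says.** The protocol states the construct and its direction several times. The background section on maternal ability to identify changes in fetal activity says that "this study aims will be the number of identified risk pregnancies, not the end point of the pregnancies". *Aim and outcome measures* gives the primary outcome as "Numbers of identified pathological conditions in pregnancies". Section 8.1 describes a "compound measure of rates of identification of risk pregnancies related to DFM" and sets a goal of a 10% increase.

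The section *Identification of perinatal risk factors in actual pregnancy* then lists the primary measures, under a lead-in saying that they are pathology that has been identified. Among them are:

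- "Fetal growth restriction (FGR) identified by ultrasound prior to birth"
- "FGR at birth, unidentified prior to birth"
- "Maternal perception of absent fetal movements for more than 24 hours before admission to hospital"
- perinatal death

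The remaining items are acute caesarean for fetal indication, non-reactive non-stress test, oligohydramnios and pathological umbilical artery flow.

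Section 8.1 builds the compound from four lines: fetal distress 8%, growth restriction below the 2.5 centile or pathological umbilical Doppler 5%, absent movements for over 24 hours 0.5%, and intrauterine death 0.02%. The stated total is 13.52%. The growth-restriction line is not divided into cases found and cases missed.

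**The concern.** A measure of identification should rise when more cases are found. A growth-restricted fetus found on ultrasound is a success on that measure, and one first recognised at birth is a failure. Counting both as the same kind of event removes the contrast that the trial is meant to show.

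Two further items sit awkwardly with the stated direction. The opening section on the Femina collaboration treats waiting over 24 hours without movements as a failure to grasp urgency. The rationale for counting is that acting early prevents adverse outcome. If counting works as intended, late presentation and death should become rarer, and each such gain lowers a compound whose goal is to go up.

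At stake is the reading of the first primary result. A real improvement in antenatal detection of growth restriction could occur and leave no trace in the primary comparison.

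**Working it through.** **Inputs** (section 8.1): fetal distress 8%, growth restriction or pathological Doppler 5%, absent movements over 24 hours 0.5%, intrauterine death 0.02%; goal a 10% increase; 538 per arm, 80% power, significance level 0.05. Assumption, because the protocol gives no split: the share *u* of the 5% line that is missed growth restriction is taken as 30%, 50% or 70%.

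**1. The plan's figures.** 8 + 5 + 0.5 + 0.02 = 13.52%, so the compound is a plain sum and reproduces. The 538 per arm does not reproduce with a two-sided test and pooled variance:

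- A relative 10% rise (13.52% to 14.87%) needs 10,460 per arm.
- An absolute 10-point rise (13.52% to 23.52%) needs 236 per arm.

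That is a separate matter. The present point does not depend on it.

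**2. Growth restriction.** Let *F* be the growth-restriction rate and *s* the share found before birth. The contribution to the compound is *F·s* + *F·(1 − s)* = *F*. The share *s* drops out. Any rise in detection changes this part by 0, and the compound stays at 13.52%.

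**3. The two small items.** Their sum is 0.5 + 0.02 = 0.52 points. With everything else held fixed:

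- both halved: 13.52 − 0.26 = 13.26%
- both eliminated: 13.52 − 0.52 = 13.00%

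If the 10% goal is relative, the gain sought is 0.10 × 13.52 = 1.35 points. The largest possible offset is then 0.52 / 1.352 = 38% of it.

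**4. A count of identified cases only.** Removing missed growth restriction, the 24-hour item and death leaves a control rate of 13.52 − 0.52 − 5*u*. If every missed case were then found, the rate would be 8 + 5 = 13.0%. The sample size formula is

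n = [1.96·√(2p̄(1−p̄)) + 0.84·√(p₁(1−p₁) + p₂(1−p₂))]² / (p₂ − p₁)².

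| Assumed missed share *u* | Control rate | Rate if all are found | Present compound changes by | Power at 538 per arm | n per arm for 80% power |
|---|---|---|---|---|---|
| 30% | 11.5% | 13.0% | 0 | 11% | 7,499 |
| 50% | 10.5% | 13.0% | 0 | 25% | 2,604 |
| 70% | 9.5% | 13.0% | 0 | 44% | 1,279 |

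The power and n columns consider a gain in growth-restriction detection alone, with no change in the other items. The items removed make up (0.52 + 5*u*) / 13.52, about 15% to 30% of the compound over this range.

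**The case against.** **Missed growth restriction may not have been meant as a component.** It appears in one list only, under a plural heading, and section 8.1 speaks of rates of identification. Such a rate needs missed cases in its denominator. The two lists also differ: section 8.1 includes scalp pH and Apgar score and omits oligohydramnios. This shows that the sections need reconciling, but it does not remove the problem. No section calls missed cases a denominator or reverses their sign, and the 8.1 table gives the prevalence of the condition, found or not. If missed cases were meant to be left out, 13.52% is too high a control rate for what remains.

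**A reader might infer that the whole effect is lost, or that the direction of the primary test cannot be interpreted.** The documents do not support that. The cancellation covers only the growth-restriction part of the 5% line, which also contains pathological Doppler. The 8% fetal distress line is untouched. Non-stress test, oligohydramnios and Doppler findings can all rise if more women are examined.

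**The 24-hour item might rise.** The protocol reports that some women make no contact even when movements are absent. If counting brings them in late instead of never, recorded cases increase. A fall is plausible on the protocol's reasoning but not certain.

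**A reader might also infer that the protocol contradicts itself on all the hard outcomes**, because it says that "relatively rare outcomes are not useful for this study" and then lists several. Only perinatal death is plainly inconsistent. Growth restriction found before birth is an identification, and the background explains why a caesarean after reduced movements may count as a positive action.

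**Accuracy.** Section 8.1 says "The goal is to increase the accuracy of maternal perception of DFM as a predictor for need of examination or intervention", which a count of pathology does not capture alone. But consultations for maternal concern and resource use are already secondary outcomes, so this is a side issue.

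**Conclusion.** The point holds in a limited form. As the sections stand, the growth-restriction part of the compound is total growth restriction, and better detection changes it by zero. This is structural and needs no assumed detection rate. Death, and less certainly the 24-hour item, can pull the compound down against its goal by at most 0.52 points of 13.52. The compound is therefore largely insensitive to one of its main intended effects and slightly reversed by two small items. It is not uninformative as a whole.

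This rests on reading the list of primary measures and the 8.1 table as describing the same compound, and on non-overlapping components, as the protocol's own sum implies. The control rates of 9.5% to 11.5% also rest on the assumed 30% to 70% missed share. An analysis plan cannot repair this without changing the primary endpoint, because the protocol itself fixes the components and the direction.

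**What to change.** - Define the primary outcome as the proportion of all randomised women with at least one listed pathology identified before birth. State explicitly how acute caesarean for fetal indication counts.
- Take growth restriction missed before birth, absent movements over 24 hours and perinatal death out of the primary and report each separately. Give missed growth restriction and death an expected direction of decrease, and leave the 24-hour item without a presumed direction.
- Report alongside the proportion of all growth restriction that was identified before birth. This keeps missed cases as the denominator and guards against a count that rises through extra testing alone.
- Align *Aim and outcome measures*, the list of primary measures and section 8.1. Restate the control rate, and the power or detectable difference at 538 per arm.

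Cost: the protocol already obtains pregnancy outcome from copies of case notes, so the data burden should be small. The event rate falls, to about 9.5% to 11.5% under the assumption above, and the stated power will look less favourable. The 11% to 44% power in the table is not a loss caused by the change, because the same gain in detection produces no difference at all in the present compound.

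### The first primary outcome is described as risk found through the mother's report of decreased movements, but its component list and planning rate are not tied to that report or to the period of counting

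*Protocol*

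**What the plan says.** **Concept.** The section on maternal ability to identify changes in fetal activity defends counting interventions as successes, for example "if a CS is performed after a mother has experienced DFM and the child was in a threatened condition". The Methods section on perinatal risk factors explains the primary outcome as consultations in which the mother's perception of DFM led to further observation or intervention. The power section calls the compound measure related to DFM.

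**Components.** The Aim section defines the outcome as "Numbers of identified pathological conditions in pregnancies" and lists conditions without a gestational window. The Methods list includes "Fetal growth restriction (FGR) identified by ultrasound prior to birth", "FGR at birth, unidentified prior to birth" and "Acute caesarean section on fetal indication (exclusive protracted delivery". Neither list requires a preceding DFM report.

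**Planning rate.** The power section's fetal distress line, 8%, combines acute caesarean with "non-reactive NST, pathological levels of fetal scap-pH or Apgar5 min ≤ 3". The compound is 13.52%.

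**Timing.** Randomisation follows the baseline questionnaire, at week 24 in the recruitment text and week 22 in the Appendix I flowchart. Then: "Women in the FMC-group will be asked to count fetal movements daily from gestational week 28". Outcomes are read from case notes with no stated extraction window, and analysis is by intention to treat.

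**The concern.** The stated concept and the operational list describe different outcomes. Under the concept, an event counts because a mother reacted to a change in movements. Under the list, it counts because it appears in the case notes.

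Three kinds of event enter under the list without any necessary link to counting:

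- **Distress first arising in labour.** The only exclusion from the caesarean item is protracted delivery.
- **Conditions found between randomisation and week 28, or earlier.** No one is counting yet.
- **Growth restriction discovered only at birth.** This is by its own wording not identified during pregnancy. If it counts in the same way as growth restriction found by ultrasound, a case that counting moves from missed to found leaves the total unchanged.

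Allocation is random, so such events should be roughly balanced between arms to the extent that counting does not affect them. The expected harm is therefore mainly dilution: the risk ratio moves towards 1 and power is lost. The planning rate adds a second problem, because it describes a composite that matches neither outcome list.

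**Working it through.** **1. The definitions side by side**

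| Component | Aim section | Methods list | Power table |
|---|---|---|---|
| Growth restriction | yes | found before birth, and found only at birth | yes, below a centile limit |
| Acute caesarean, fetal reasons | yes, no exclusion stated | yes, protracted delivery excluded | yes, protracted birth excluded |
| Non-reactive NST | yes | yes | yes |
| Oligohydramnios | yes | yes | **no** |
| Abnormal umbilical flow | yes | yes | yes |
| Absent movements over 24 hours | yes | yes | yes |
| Death | perinatal | perinatal | intrauterine |
| Scalp pH | **no** | **no** | **yes** |
| 5-minute Apgar | **no** | **no** | **yes** |
| Preceding DFM report required | no | no | no |

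Scalp pH and Apgar are measured in labour and after birth, so the planning rate contains such events.

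**2. The planning rate.** 8 + 5 + 0.5 + 0.02 = 13.52, as stated. The fetal distress share is 8/13.52 = 59%. The protocol does not split it into antepartum and intrapartum.

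**3. Gap before counting.** 28 − 24 = 4 weeks by the text; 28 − 22 = 6 weeks by the flowchart. This is elapsed time, not a share of events.

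**4. The stated sample size.** With the usual two-proportion formula (two-sided 0.05, 80% power),

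n per arm = [1.96·√(2p̄(1−p̄)) + 0.84·√(p₁(1−p₁) + p₂(1−p₂))]² / (p₂−p₁)²

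- 10% read as absolute (13.52% to 23.52%): 236 per arm.
- 10% read as relative (13.52% to 14.87%): 10,460 per arm.

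Neither gives 538. That is a separate problem and neither supports nor weakens this point. To illustrate dilution I use the effect that 538 per arm does correspond to: 13.52% to 19.88%, risk ratio 19.88/13.52 = 1.47 (the formula gives 539).

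**5. Dilution, for an assumed share f of events that counting cannot change**

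- Events left in: p₁ = 13.52%, p₂ = 13.52% × [f + (1−f) × 1.47].
- Events taken out: p₁ = 13.52% × (1−f), p₂ = 1.47 × p₁.

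| f (assumed) | Left in: power at 538 | Left in: n per arm | Taken out: power at 538 | Taken out: n per arm |
|---|---|---|---|---|
| 0 | 80% | 539 | 80% | 539 |
| 10% | 72% | 656 | 75% | 611 |
| 25% | 57% | 922 | 66% | 755 |
| 50% | 31% | 1,990 | 47% | 1,187 |
| 59% (whole distress line) | 22% | 2,938 | 39% | 1,478 |

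At every non-zero f, taking the events out costs less power than leaving them in. No row is an estimate, because the protocol does not give f.

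**The case against.** **The DFM link may already do the work.** Read strictly, the sentences tying the outcome to the mother's perception would exclude distress in labour with no prior DFM consultation, and diagnoses made before counting. This stands in part. A reader might infer that the protocol positively counts conditions found before week 28, but that is silence, not a statement. The strict reading cannot be squared with the caesarean item's single exclusion, or with scalp pH and Apgar in the planning rate.

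**The outcome is not open-ended.** A reader might say it has no stop at all. That is not supported: several items end before birth, at birth, at admission or in the perinatal period. What is absent is a link to DFM or to the counting period.

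**Counting may affect events in labour.** The section on advantages and disadvantages says counting might reduce asphyxia and might increase obstetric interventions. This stands. It would be too strong to say that labour events cannot respond, or that a fixed portion of the composite is inert. Any assumed labour share has no anchor in the documents, and the distress line also holds non-reactive NST.

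**A cut at onset of labour would be worse.** This also stands. Induction may follow a DFM report, and start of delivery is itself a secondary outcome, so the cut would condition on something that counting can change. It would also drop growth restriction found at birth and deaths during or after labour.

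**Windows are commonly left to the SAP.** This is fair for extraction detail. But the protocol itself fixes the component list, its one exclusion, the planning rate and the time of randomisation. Narrowing the composite in a SAP would leave the 13.52% describing a different outcome.

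**Conclusion.** The point holds as an inconsistency within the protocol. The primary outcome is justified as risk identified through maternal perception of DFM, but neither the two component lists nor the prevalence table applies that condition. Distress arising in labour enters through the caesarean item. The planning rate includes scalp pH and Apgar and omits oligohydramnios. Randomisation precedes counting by about four weeks or more, with no limit on when a condition must be found.

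The likely consequence is dilution and lost power. That rests on the inference that most such events are little affected by counting, which is reasonable but not stated in the protocol. Its size is unknown. The fetal distress line is 59% of the planning rate, but that is not the intrapartum share. On the illustrative risk ratio of 1.47, power at 538 per arm is 72% if 10% of events cannot respond and 31% if half cannot. The documents do not support going further and saying that a real benefit would be missed.

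**What to change.** 1. Keep the week-24 baseline questionnaire, but draw the allocation just before week 28. Diagnoses and deliveries in the gap then precede randomisation, and no randomised woman has to be excluded afterwards. Reconcile the flowchart's week 22 with the text.
2. In both arms, count only components first identified from week 28.
3. Use one composite definition in the Aim, Methods and power sections. For each component, record its date and whether a DFM consultation preceded it. State explicitly how growth restriction found only at birth is handled, and whether death means perinatal or intrauterine.
4. Report scalp pH, Apgar, and caesarean for distress in labour without a preceding DFM consultation as secondary outcomes.
5. Do not cut all events at onset of labour, because induction may itself follow a DFM report.
6. Restate the 13.52% planning rate for the reconciled composite, and the sample size with it.

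**Cost.** Protocol wording, a date and a DFM field per component on the case-note form, and a later allocation step. The event rate falls: in the illustration, removing 10% to 50% of events raises the requirement from 539 to between 611 and 1,187 per arm, against 656 to 1,990 if the same events stay in. Women who deliver before week 28 are not randomised.
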